## Abstract

**Background:**

Ankle sprain is a common clinical disease, which has the highest incidence rate among joint and ligament injuries. And acute ankle sprains can easily develop into chronic ankle instability, thereby increasing the difficulty of treatment. The current clinical guidelines for post-acute ankle sprains are still controversial. Pain and functional impairment are the most significant symptoms after ankle sprain. The main purpose of this study is to explore the safety and effectiveness of the intervention of integrated traditional Chinese and Western medicine rehabilitation programs on post-acute ankle sprains.

**Methods:**

This study is a single center, prospective, intervention randomized controlled trial with a control group. 174 patients of 18–35 years old with post-acute ankle sprain will be included. A randomized controlled study is conducted and divided into a control group and an experimental group. The control group receive routine treatment, while the experimental group receive integrated traditional Chinese and western medicine rehabilitation programs. The intervention lasted for a total of 2 weeks. The main outcome measures are Visual Analog Scale and Short Form McGill Pain Questionnaire; the secondary outcome measures are the Foot Ankle Ability Assessment Scale, AOFAS Ankle Posterior Foot Scale, torque and gait. This study protocol aims to evaluate the safety and effectiveness of integrated traditional Chinese and western medicine rehabilitation programs by comparing the results of two groups before and after treatment. This protocol will follow the SPIRIT guidance.

**Discussion:**

At present, there is a lack of rehabilitation management for post-acute ankle sprains. Therefore, this study has the potential to improve the healthcare for post-acute ankle sprains patients and might be used for future standardized evidence-based rehabilitation concepts.

**Trial registration:**

The trial was registered at Chinese Clinical Trial Registry https://www.chictr.org.cn/showproj.html?proj=234465 (Registration No.: ChiCTR2400087456). Date: 2024-07-29.

## Introduction

Ankle sprain is one of the most common injuries during our clinic career. Ankle sprain often occurs with foot inversion or adduction, and most often happens at the lateral ankle [1]. The risk factors for ankle sprains include limited range of motion of the ankle joint, poor coordination function, weakened balance function [2,3], decreased proprioception and insufficient muscle strength [4–6], and even decreased cardiovascular and pulmonary function [4,7]. Exercise is the highest risk factor for ankle sprain occurrence [8]. About 40% of patients develop into chronic ankle sprains with persistent symptoms [9,10]. Usually, we consider the acute period refers to the first 1–2 weeks after injury. And, the term “post-acute” replace "subacute" to characterize the time after the acute period to the 12-month point. Literature has found that 60% of individuals achieve resolution of activity limitations and participation restrictions by the 12-month point [11]. And often we tend to refer to chronic ankle sprain as ankle instability which prolongs patient pain, affects patient’s life, enlarges treatment costs and social burden [12]. Thereby, we consider the post-acute period as an important phase for ankle sprain recovery.

Due to the fact that the ankle joint is an important load-bearing bone joint, its stability and function are crucial for daily activities and exercise. Although there are currently multiple treatment methods for ankle sprains, there are differences in the efficacy and safety of different methods [7,13]. The study of effective treatment methods for post-acute ankle sprains has important clinical significance.

When ankle sprain occurs, the “RICE” principle (rest, ice application, compression and elevation) can be used for treatment. The initial focus of the rice principle was on reducing pain while restoring strength and range of motion. However, the evidence supporting this method is limited [7,14]. Physical therapy is also believed to promote the recovery process, but the effect is slow and time-consuming [15]. Evidence from RCTs of moderate quality indicate that daily physical therapy is better tolerated than longer, less frequent physical therapy sessions [16]. Extracorporeal shock wave is considered one of the treatment methods for soft tissue injuries in the feet and ankles [17,18]. The sustainability of ESWT treatment efficacy may depend on energy levels and the severity of ankle sprains, which should be studied in future research [19]. From the perspective of traditional Chinese medicine treatment, acupuncture is considered a complementary and alternative therapy to modern medicine [20,21] and Previous systematic reviews have shown that acupuncture treatment for ankle sprains has a certain therapeutic effect [21–23]. However, the evidence for acupuncture treatment of ankle sprains is still uncertain due to significant heterogeneity [22,24]. Manual training can help recover from ankle sprains, which is also recommended in the guidelines [25]. Manual training can alleviate pain and improve gait [26]. The involvement of neuromuscular training programs in manual training can effectively prevent the recurrence of ankle sprains [27]. considering that neuromuscular and proprioceptive training is safe and effective, the guidelines also recommend implementing neuromuscular training as soon as possible after ankle sprains [28–30]. Surgery is one of the strategies for treating ankle sprains. Kerkhoffs et al. found similar functional and subjective symptom outcomes when comparing surgical intervention and conservative treatment for lateral ankle ligament complex injuries [31]. Severe tibiofibular syndesmosis injury or combined with triangular ligament rupture can benefit from surgical fixation. Ankle joint fracture combined with lower tibiofibular joint injury requires surgical fixation of the fracture. However, repairing ligament injuries simultaneously is controversial [32].

In a word, there are many methods to deal with an ankle sprain. Traditional treatment methods such as “RICE” principle will be first adopted which can alleviate pain and swelling to a certain extent, but more effective treatment methods are needed for serious situations such as ligament damage. However, the latest evidence-based clinical guidelines do not recommend the best treatment for ankle sprains [7]. Based on the above reasons, we draft a protocol on the integrated traditional Chinese and western medicine rehabilitation programs (TCAWM) for the treatment of post-acute ankle sprains. Our clinical research aims to evaluate whether TCAWM can be more effective treatment methods for post-acute ankle sprains, in order to improve the rehabilitation effect and quality of life of patients.

## Methods

### Design

The study is a randomized controlled trial (RCT). A total of 174 post-acute ankle sprain patients will be recruited and randomly divided into the intervention group and the control group at a ratio of 1:1. Recruitment of eligible patients will begin from January 2025. Participants of the intervention group will be treated with TCAWM and participants of the control group will be treated with routine treatment. The whole study period will be 2-week including baseline and 2-week treatment. The study design is illustrated in the flow chart in Fig 1. The study protocol was approved by the Regional Ethics Review Committee of Shuguang Hospital (number: 2024-1535-118-01).

**Fig 1 pone.0318535.g001:**
[figure not shown]
Study flow chart.

### Participant

Patients will be recruited in Shuguang Hospital, through bulletin board posts and surrounding communities through advertising (posting notices and online advertisement). All eligible participants will be tested in Shuguang Hospital and operated by doctor responsible for recruitment. Ensuring consistency and replicability in our study, this protocol will include structured assessment tools that will be administered by trained research staff. All personnel involved in the screening process will undergo comprehensive training to ensure they understand the inclusion and exclusion criteria thoroughly. This training will cover how to administer the screening tools, interpret responses, and make decisions based on the criteria. Meanwhile, we will maintain detailed records of the screening process, including the number of individuals screened, the reasons for exclusion, and any challenges encountered. This documentation will be included in our final report to provide transparency and facilitate replicability. The eligible participants must meet the following criteria.

#### Diagnostic criteria

The participant needs to meet the diagnostic criteria. Referring to the "Diagnostic and Therapeutic Efficacy Standards for Traditional Chinese Medicine Diseases" issued by the National Administration of Traditional Chinese Medicine and the Clinical Practice Guidelines for the International Classification of Function, Disability, and Health of the American Physical Therapy Association Orthopedic Branch for Ankle Ligament Sprains (2021 Edition), it is proposed that: ① There is a clear history of ankle trauma; ② After spraining, there is obvious tenderness or subcutaneous bruising in the ankle joint, accompanied by swelling and pain, limited weight-bearing, and limping; ③ Limited joint mobility; ④ Ottawa principle is negative, X-ray examination shows no fracture or dislocation.

### Inclusion criteria

① Those who meet the diagnostic criteria for ankle sprains, in the post-acute period, and have an injury grade of I or II [33];

② Age range from 18 to 35 years old, regardless of gender [34–37];

③ Cumberland Ankle Instability Scale score ≤ 24 points;

④ Those who have not received any other treatment before treatment and are willing to receive conservative treatment shall sign an informed consent form.

### Exclusion criteria

① Both ankles sprained;

② Individuals with skin damage or skin disease in the affected area;

③ Ankle fracture, dislocation, severe osteoporosis and diseases that may affect muscle strength, such as diabetes and rheumatoid arthritis;

④ Subjectively unwilling to accept the experimenter by the patient;

⑤ Use antipyretic, analgesic, sedative, or steroid drugs in the past week;

⑥ Have a history of cardiovascular and cerebrovascular diseases, central nervous system tumor diseases, mental illness, or head injury;

⑦ Individuals with contraindications for physical therapy such as metal objects in the ankle.

### Intervention

A randomized controlled study is conducted and divided into a control group and an experimental group. The control group receive routine treatment, while the experimental group receive the integrated traditional Chinese and western medicine rehabilitation programs (TCAWM), once a day and five times a week, for a total of two weeks of intervention. The intervention schedules for each group are shown in Table 1 Intervention Schedules.

**Table 1 pone.0318535.t001:** Intervention schedules.

Period	Screening	Allocation	Intervention		Follow up
Week	-2week	-1week	0week	2week	3 months
Eligibility screening	✓				
Informed consented	✓				
Demographics	✓				
Diagnosis	✓				
Medical history	✓				
Randomization and allocation		✓			
VAS			✓	✓	✓
SF-MPQ			✓	✓	✓
FAAM			✓	✓	✓
AOFAS Ankle Posterior Foot Scale			✓	✓	✓
Torque			✓	✓	✓
Gait			✓	✓	✓
Adverse events				✓	✓

VAS, Visual Analog Scale; SF-MPQ, Short form McGill Pain Questionnaire; FAAM, Foot and Ankle Ability Assessment Scale; AOFAS Ankle Posterior Foot Scale, American Orthopedic Foot and Ankle Association Ankle Posterior Foot Scale.

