### Randomization and allocation concealment

The patients who meet the diagnosis of post-acute ankle sprain and sign informed consent will be randomly assigned to control group and intervention group at a ratio of 1:1. Randomization will be computer generated by independent and uninformed statistical experts. Managers who do not participate in the recruitment and treatment place each number in an opaque envelope and keep it. After screening the patients, the doctor responsible for recruitment will contact the administrator who will send the file to the eligible participants and inform them of the allocation.

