### Blinding

Due to the nature of the intervention, therapists and participants cannot be blinded. So we provide standard training to patients before they receive intervention, including informing them of the intervention methods and specific implementation, as well as self-assessment methods (VAS、SF-MPQ) for the efficacy after intervention; We have not only established self-assessment during the evaluation process, but also established third-party objective evaluations, and the third-party evaluators will also receive standard training including standardized use of equipment for evaluation to reduce the impact of intervention expectations. During the study, statisticians, administrator, data collectors and result evaluator will be blinded. After the statistics, the blinding method will be broken.

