### Limitation

Despite the potential strengths, there are some limitations in our trial. Firstly, in this study, the intervention is a non-drug therapy, which cannot be ideally implemented in accordance with the provisions of double-blind. However, the strict management of researchers, data managers and statisticians in this study will help us to reduce performance bias. Secondly, the planned short treatment period to minimize dropout rates may affect the results of this study.Thirdly, due to insufficient preliminary data to determine the sample size, we have designed this experiment as a single center preliminary study. In addition, the sample selection for this protocol is between the ages of 18 and 35, further studies in various groups with a greater age range such as childern and olders are recommended. Fourthly, the patients cannot be blinded due to the particularity of treatment. Patients will know whether they had received additional treatment, which, in some cases, may have increase the risk of dropout in control patients. Finally, this is an exploratory study that does not involve long-term follow-up to observe long-term treatment outcomes and adverse reactions. For this reason,we will add a plan for participant follow-up after the protocol ends which could help assess the durability of intervention effects.

Nevertheless, the results of this study are expected to provide preliminary evidence on the effectiveness and acceptability of the integrated traditional Chinese and Western medicine in the treatment of grade I and grade II post-acute ankle sprains, and serve as the basis for further research.

The authors appreciate their colleagues in Shuguang Hospital Affiliated to Shanghai University of Traditional Chinese Medicine for their full support in recruiting and treating patients. The authors appreciate the efforts and help of investigators participating in this trial. The authors appreciate [name] for his guidance.

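### Table 1 places randomisation at week -1 and the first outcome measurement at week 0, so the only baseline for the self-rated, unblinded primary outcomes is a post-randomisation value

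*Protocol article*

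**What the plan says.** Table 1 (protocol article, Intervention) has dated columns. The row "Randomization and allocation" carries one tick, in the allocation column at week -1. The six outcome rows (VAS, SF-MPQ, FAAM, AOFAS, torque, gait) are first ticked at week 0, under the intervention heading, and have no tick at week -2 or week -1. Demographics, diagnosis and medical history are ticked at week -2.

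The other relevant statements are:

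- Randomization and allocation concealment: once a patient has been screened, the recruiting doctor will "contact the administrator who will send the file to the eligible participants and inform them of the allocation". No date is given for this step.
- Blinding: "Due to the nature of the intervention, therapists and participants cannot be blinded". The same section describes training in "self-assessment methods (VAS、SF-MPQ) for the efficacy after intervention", so the two primary outcomes are rated by the participant. Outcome evaluators are to be blinded.
- Limitation: "Patients will know whether they had received additional treatment".
- Design: "The whole study period will be 2-week including baseline and 2-week treatment". Baseline is thus counted with the treatment period and not with screening.
- Abstract, Methods: the programme is to be evaluated "by comparing the results of two groups before and after treatment".
- Statistical analysis: intention to treat for the primary assessment, analysis of variance for quantitative data, and multiple imputation for missing values.

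**The concern.** A baseline is useful in a randomised comparison because the allocation cannot have affected it. Once participants know their arm, a self-rated pain score can move with hope, disappointment or a wish to show room for improvement. Any average difference between the arms at week 0 is then partly a consequence of allocation and no longer only chance. Subtracting that value or adjusting for it carries the difference into the estimated treatment effect.

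The exposure is greatest for VAS and SF-MPQ. Torque and gait are measured by blinded evaluators, but they depend on the participant's effort and may be affected to a lesser degree.

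There is a second, smaller consequence. A participant who withdraws between week -1 and week 0 belongs to the intention-to-treat set but has no outcome value at all, so imputation would have only the screening covariates to work from.

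**Working it through.** **Order of events.** Set side by side, the sections give this sequence:

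| Step | Where stated | Timing |
|---|---|---|
| Screening, demographics, history | Table 1 | week -2 |
| Randomisation and allocation | Table 1 | week -1 |
| Participant told the arm | Randomization and allocation concealment | undated; follows screening, part of the allocation step |
| First VAS, SF-MPQ, FAAM, AOFAS, torque, gait | Table 1 | week 0 |
| Second measurement | Table 1 | week 2 |

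No section schedules an earlier outcome measurement, and none withholds the allocation until the week-0 assessment is done. Week 0 is the only possible baseline, and it comes after randomisation.

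**The plan's own figure.** Inputs from Sample size: means after two weeks 0.25 (control) and 0.04 (experimental), SD 0.45, α = 0.05, β = 0.2.

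- Planned difference: 0.25 − 0.04 = 0.21 cm.
- n per group = 2 × (1.960 + 0.842)² × 0.45² / 0.21² = 72.08. The stated 72 is reproduced.
- 72 × 1.2 = 86.4, rounded up to the stated 87.

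This calculation compares two means after treatment and does not use a baseline value. It serves here only to give the scale of the planned effect.

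**How a week-0 shift enters the estimate.** Let τ be the true effect (experimental minus control) at week 2. Let d be the between-arm difference in mean week-0 VAS caused by knowing the arm, and β the slope of the week-2 value on the week-0 value. If the shift does not persist to week 2:

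- week-2 means alone: estimate = τ
- change score: estimate = τ − d (slope 1)
- baseline-adjusted: estimate = τ − β × d

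The break-even values against the planned 0.21 cm are 0.21 / 1 = 0.21 cm for a change score and 0.21 / 0.5 = 0.42 cm for an assumed slope of 0.5. They show what shift would be needed to equal the planned effect, not what shift is likely.

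**Illustration over a range.** None of these settings is in the article except the SD, which it gives for planning the week-2 comparison: 72 analysed per group, SD 0.45 at both visits, τ = 0, correlation r between visits of 0.3, 0.5 or 0.7, and |d| of 0.05, 0.10 or 0.20 cm. With equal SDs, β = r. Standard errors are 0.45 × √(2(1 − r)) × √(2/72) for the change score and 0.45 × √(1 − r²) × √(2/72) for the adjusted analysis.

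One case in full, d = 0.10 and r = 0.5:

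- Change score: SE = 0.45 × 1 × 0.1667 = 0.075; bias/SE = 0.10 / 0.075 = 1.33; two-sided rejection rate 26.6%.
- Adjusted: SE = 0.45 × 0.866 × 0.1667 = 0.065; bias/SE = 0.05 / 0.065 = 0.77; rejection rate 12.0%.

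| Shift (cm) | Change score, r = 0.3 / 0.5 / 0.7 | Baseline-adjusted, r = 0.3 / 0.5 / 0.7 |
|---|---|---|
| 0.05 | 8.7% / 10.2% / 13.8% | 5.5% / 6.7% / 10.0% |
| 0.10 | 20.3% / 26.6% / 40.6% | 7.0% / 12.0% / 25.7% |
| 0.20 | 61.6% / 76.0% / 93.1% | 13.4% / 33.7% / 74.3% |

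These are rejection rates in either direction for a nominal 5% test. Post-treatment means alone stay at 5% under the same assumptions.

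**The case against.** Several points on the other side are fair.

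- **Disclosure before week 0 is inferred.** The randomisation section gives no date and the flow chart (Fig 1) is not shown. A reader might take it as stated that participants already know their arm when first measured. The article does not say so; it follows from the order in Table 1 and from the absence of anything that delays disclosure. The inference is reasonable, but it is an inference.
- **The only comparison the plan quantifies does not use baseline.** Sample size rests on means after two weeks, and Statistical analysis says no more than analysis of variance. The abstract's before-and-after wording suggests a use of baseline without defining it. The bias is therefore conditional on the analysis, and this limit stands.
- **The direction is unknown.** A reader might infer that the schedule favours the experimental arm. If hopeful experimental participants report less pain at week 0, or disappointed controls report more, d is negative and the apparent benefit shrinks. A reporting shift that lasts to week 2 cancels in a change score. Inflation is possible too, if d is positive. The article supports neither direction.
- **The size is unsupported.** Nothing in the article makes a shift of 0.21 or 0.42 cm plausible.
- **Dropout.** A reader might infer that the authors expect more dropout among controls. The Limitation section says only that this risk may rise in some cases, and it does not mention the interval between week -1 and week 0.
- **Missing data.** Early withdrawals would still have screening covariates, and a baseline value would not replace their missing week-2 outcome. The loss is of useful information for imputation, not of all information.

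The sequence in the printed schedule remains. It is stated rather than left out by condensation, and an analysis plan cannot change when data were collected.

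**Conclusion.** The point holds as a defect of sequence. As scheduled, the only baseline for the two self-rated, unblinded primary outcomes is taken after randomisation and, on the order given, after the participant can know the arm. An analysis of change or one adjusted for baseline would be biased by slope × shift, with unknown sign; a comparison of week-2 means alone would not be.

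The size cannot be derived from the article. Under the assumptions in the working, a 0.10 cm shift, about half the planned 0.21 cm, takes the error rate to 20.3–40.6% for change scores and 7.0–25.7% with adjustment. A 0.05 cm shift takes it to 8.7–13.8% and 5.5–10.0%. The assumptions are the shift, the correlation, equal SDs at both visits, 72 analysed per group and no persistence to week 2.

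This should be fixed because re-ordering is cheap and a contaminated baseline cannot be repaired afterwards. It does not show that the trial's result will be biased or in whose favour.

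**What to change.** Complete all six baseline outcome measures before the allocation is released. The same week-0 visit, just before treatment starts, is preferable. Measuring at week -1 would also precede allocation, but it would leave up to a week in which pain could change before treatment begins.

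Define that pre-allocation value as baseline. Move the randomisation tick in Table 1 so that it follows the baseline assessment, and state in Randomization and allocation concealment that the administrator releases the allocation only once the baseline assessment is recorded. If practice already measures first, Table 1 is wrong and needs only that correction.

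The cost is small. No procedure is added, but the allocation has to be released at the visit, and a few participants who are assessed may not go on to be randomised.
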